### Outcomes

#### Primary outcome

Recruitment rates for the whole 24-month recruitment period will be reported overall and per recruiting site. The average recruitment rate per month and in total over the formal monitoring period will be reported.

The study recruitment period is 24 months. To show that patient recruitment targets for a phase III RCT can be met within an adequate timeframe, a ‘steady state’ of recruitment should be observed. In this feasibility study, formal monitoring of recruitment will begin from the start of the patient recruitment where an average of two patients per month must be randomised over the remaining recruitment period in order to demonstrate a ‘steady state’ of recruitment.

#### Secondary outcomes

Incidence of patient-reported acute (0–3 months) and long-term toxicity (>3 months) and impact on QoL determined by EPIC-26 (prostate cancer related QoL and functional outcomes), EORTC QLQ-C30 (general QoL score) and IPSS (urinary and sexual functional outcomes) measurements (key secondary endpoint).Incidence of clinician-reported treatment toxicity as per CTCAE V.5.0.Other feasibility endpoints include screening log summaries, treatment and questionnaire compliance, withdrawal rate and reasons for non-recruitment.

#### Exploratory outcomes

MRI biomarkers at 1 month and 1 year post-treatment predictive of toxicity based on PROMs.Hypoxia levels based on a hypoxia associated gene signature obtained from the presalvage RT biopsy correlated with MRI biomarkers.Changes in the levels of inflammatory cytokine signatures from urine and blood obtained at baseline and after reirradiation in relation to PROMs.Multiple measures of image quality and reproducibility of prostate functional imaging (eg, diffusion coefficient values from IVIM sequences) for measuring tumour biology will be summarised.

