**Methods and analysis:**

The primary endpoint of the RO-PIP feasibility study is to evaluate the patient recruitment potential over 2 years to a trial randomising to either SBRT or HDR-BT for patients who develop local recurrence of prostate cancer following previous radiation therapy. The aim is to recruit 60 patients across 3 sites over 2 years and randomise 1:1 to SBRT or HDR-BT. Secondary objectives include recording clinician and patient-reported outcome measures to evaluate treatment-related toxicity. In addition, the study aims to identify potential imaging, genomic and proteomic biomarkers that are predictive of toxicity and outcome based on hypoxia status, a prognostic marker of prostate cancer.

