#### PROMs assessment

Changes in patient-reported health-related quality of life (QoL)/PROMs will be assessed using the following validated questionnaires: Expanded Prostate Cancer Index Composite-26 (EPIC-26) (prostate cancer-related QoL and functional outcomes), European Organization for the Research and Treatment of Cancer Quality of Life Questionnaire (EORTC QLQ)-C30 (general QoL Score) and IPSS (urinary and sexual functional outcomes). The specific time points for these evaluations are:

Baseline assessment (prior to salvage treatment).1 month post-treatment completion.3 months post-treatment completion.6 months post-treatment completion.12 months post-treatment completion.24 months post-treatment completion.

The PROMs and quality-of-life assessments will not require a separate face-to-face meeting as these will be posted out to the participants. Follow-up after 2 years will be according to local policy.

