#### Translational MRI assessment

All patients will have three multiparametric MRIs (including standard anatomical sequences and functional sequences), which will be paired with PROMs assessments at the same time points (at baseline and then post-treatment at 1 month and 1 year). The purpose of this imaging component is fourfold:

To optimise a multiparametric MRI scanning protocol across three institutions incorporating intravoxel incoherent motion (IVIM), dynamic contrast-enhanced imaging and blood oxygenation level dependent sequences.To evaluate image quality and reproducibility of prostate functional imaging for detecting tissue perfusion and hypoxia.To investigate prostate and pelvic anatomical and functional imaging changes related to prostate reirradiation and how this relates to patient-reported toxicity side effects (determined by PROMs).To study the multiparametric MRI changes seen in the prostate in association with biopsy derived hypoxia-associated gene signature.

MRI scans done within the research study will be stored on the Leeds Teaching Hospitals Picture Archive and Communication System (PACS) server and on the local hospital PACS server where the images were obtained.

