#### Statistical analysis

As this is a feasibility study, it will not involve hypothesis testing to identify whether the intervention has had an impact. Instead, data analysis will be descriptive and involve summary statistics. The analysis of all primary endpoint and all secondary endpoints relating to recruitment and withdrawals from the trial will take place at the end of the 24-month recruitment period. Final analysis of all other endpoint data will be carried out 6 months after the final participant has been randomised.

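### The exploratory MRI outcome calls the 1-year scan predictive of patient-reported toxicity, although only the 24-month questionnaire follows it, and it does not list the baseline scan

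*Protocol article*

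**What the plan says.** Under Exploratory outcomes, the protocol article lists "MRI biomarkers at 1 month and 1 year post-treatment predictive of toxicity based on PROMs". The line names two post-treatment scans. It does not name the baseline scan, and it does not say which questionnaire is to be predicted.

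The section Translational MRI assessment states that "All patients will have three multiparametric MRIs", "which will be paired with PROMs assessments at the same time points (at baseline and then post-treatment at 1 month and 1 year". Table 1 shows the same schedule. That section describes the purpose in the language of association: "functional imaging changes related to prostate reirradiation and how this relates to patient-reported toxicity side effects (determined by PROMs".

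The section PROMs assessment sets questionnaires at baseline and at 1, 3, 6, 12 and 24 months after treatment completion. Secondary outcomes splits patient-reported toxicity at 3 months: "Incidence of patient-reported acute (0–3 months) and long-term toxicity (>3 months". The abstract gives the broader aim, which is to "identify potential imaging, genomic and proteomic biomarkers that are predictive of toxicity and outcome based on hypoxia status".

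On timing, the Statistical analysis section says of everything except the recruitment and withdrawal endpoints: "Final analysis of all other endpoint data will be carried out 6 months after the final participant has been randomised".

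**The concern.** Prediction needs the marker to come before the outcome. The only MRI–questionnaire pairing that the article describes is at the same visit, yet the listed outcome speaks of prediction. For the 1-year scan this matters, because nearly all the patient-reported toxicity is recorded before it or alongside it. Tissue change seen at 1 year in a man who already has symptoms may be a consequence or an accompaniment of those symptoms' cause, and says nothing about whether the scan could have forecast them.

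The article's list of strengths says that the translational work should identify candidate markers for a phase III trial. A 1-year finding labelled predictive could be carried forward on that basis. Meanwhile the baseline scan, the only one available before treatment, is absent from the outcome line that speaks of prediction.

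**Working it through.** The plan states no figure on this point, so the check sets the two schedules side by side and then counts who could have the later data.

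**1. Order of scans and questionnaires** (PROMs assessment, Translational MRI assessment, Table 1; months after treatment completion)

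| MRI | Same-visit questionnaire | Post-treatment questionnaires before it | Questionnaires after it |
|---|---|---|---|
| Baseline | baseline | none | 1, 3, 6, 12, 24 |
| 1 month | 1 | none | 3, 6, 12, 24 |
| 12 months | 12 | 1, 3, 6 | 24 |

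The acute window (0–3 months) holds the 1- and 3-month questionnaires, and both precede the 1-year scan. The long-term window (beyond 3 months) holds those at 6, 12 and 24 months. Of these, one precedes the 1-year scan, one coincides with it and one follows it.

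**2. Who could have later data at the final analysis**

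Inputs from the article: 60 patients, 24 months of recruitment, final analysis 6 months after the last randomisation. If recruitment takes the planned 24 months, the analysis falls at month 24 + 6 = 30.

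Assumptions, not in the article: even accrual, so 60/24 = 2.5 patients per month; a lag *d* of 0 to 2 months from randomisation to treatment completion; no dropout.

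Patients who could have reached follow-up month *m* by month 30: 60 × min(24, 30 − *d* − *m*)/24.

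| Follow-up month | *d* = 0 | *d* = 1 | *d* = 2 |
|---|---|---|---|
| 3 | 60 | 60 | 60 |
| 6 | 60 | 57.5 | 55 |
| 12 | 45 | 42.5 | 40 |
| 24 | 15 | 12.5 | 10 |

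For example, for *m* = 24 and *d* = 2: 60 × (30 − 2 − 24)/24 = 60 × 4/24 = 10. A lag of 3 months would give 60 × 3/24 = 7.5.

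**3. Reading the two together**

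- The 1-month scan has genuinely later questionnaires in most patients at month 30: all 60 at 3 months, 55 to 60 at 6 months and 40 to 45 at 12 months.
- The 1-year scan itself would be available in about 40 to 45 patients, each with a same-visit questionnaire, but only 10 to 15 would have the one questionnaire that follows it. For the other roughly 30 (45 − 15 or 40 − 10), the 1-year scan could be compared only with scores taken at the same time or earlier.

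**The case against.** The strongest reply is that the article never says that same-visit pairs will be analysed as prediction. The pairing can be read as a visit schedule, the imaging section speaks only of how changes relate to toxicity, and the choice of model belongs in a fuller document that is not shown. This largely stands: mislabelling is a risk that the wording allows, not a plan that it states. It does not remove the point, because the outcome as listed names the 1-year scan as predictive, and no later modelling detail can make a 12-month scan precede a score taken by month 12.

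Three stronger readings are tempting, and the documents do not support them:

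- *Both scans yield only same-time association.* This is not so for the 1-month scan, which four of the five post-treatment questionnaires follow.
- *The baseline scan is left out of the study, or will never be tested as a predictor.* It is acquired in every patient, and an aim of studying change requires it. It is missing from one outcome line.
- *The 1-year scan comes after most long-term toxicity assessments.* It comes after one of three.

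The sentence could also be read with the time points attached to toxicity, as markers of toxicity at 1 month and at 1 year. On that reading the baseline scan is not excluded. The ambiguity is itself worth removing, since the two readings lead to different analyses.

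Finally, the count of 10 to 15 measures how little later data the 1-year scan would have at month 30. It does not by itself show that association will be mislabelled.

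**Conclusion.** The point holds for the 1-year scan and for the wording of the outcome. That scan cannot predict acute toxicity or the 6- and 12-month scores. Its only later score, at 24 months, would exist for about 10 to 15 of 60 patients at the month-30 analysis, given even accrual, recruitment completed in 24 months and a lag of 0 to 2 months; dropout would lower this. The outcome line also fails to list the only pre-treatment scan. It therefore leaves room for same-time or backward-looking association to be reported as prediction.

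The severity is minor. The outcome is exploratory, the analysis is descriptive, and neither the primary outcome nor the key secondary endpoint is affected.

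**What to change.** Reword the exploratory outcome so that each predictor is tied to a later outcome:

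- Predictors: the baseline MRI, and the 1-month MRI or its change from baseline, each against questionnaires taken after the scan concerned and taking the baseline questionnaire score into account.
- 1-year MRI: a predictor of the 24-month score only.
- 1-year MRI against scores up to 12 months, and all other same-visit comparisons: described as association.
- Any analysis of 24-month scores, for whichever scan: held until those data are complete.

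No new scan, visit or patient is needed. The cost is the rewording, plus a delay for every 24-month result. The article gives study completion as September 2026, 24 months after the planned end of recruitment. On the same assumptions, 60 × (48 − *d* − 24)/24 gives 55 to 60 patients reaching 24 months by then, so the delay fits largely within the planned study duration.

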### Sample size

This is an exploratory feasibility study, and there is no informative data in the published literature on which to base a sample size calculation. Therefore, a formal statistical power calculation has not been performed. Feasibility studies are not usually sufficiently powered to provide estimates of effect size, but instead aim to determine the feasibility of specific study aspects and to enable estimation of sample size parameters to inform future studies. For this feasibility study, we plan to recruit 60 patients in total (ie, 30 to each treatment arm) from three UK hospitals (Leeds Cancer Centre, The Christie and Mount Vernon Cancer Centre), all of which are high-volume tertiary prostate cancer treatment centres. This sample size has been informed by the National Institute of Health Research guidance on feasibility sample sizes and the toxicity outcome data from a recent systematic review.^13 24^ Few studies have evaluated PROMs feasibility, establishing the need for this trial.^25^ It is estimated that this number of participants will provide an adequate sample to estimate the toxicity rates for the key secondary endpoint in each arm (ie, 30 per arm).^26 27^ Recruiting 60 patients over 2 years, across 3 centres, would mean an average recruitment rate of 1 patient per centre per month. This information, combined with the estimated toxicity rates from the study, will be used to determine feasibility of a subsequent larger scale RCT.

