### Recruitment

Overall, 60 patients will be recruited over a 24-month period, approximately 2–3 patients per month (across 3 sites).

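### The planned recruitment rate is 0.83, not 1, per centre per month, and the two-a-month criterion is met at 48 patients without the protocol saying that this is intended

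*Protocol article*

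**What the plan says.** The recruitment target is the same wherever it appears. The abstract gives it as "The aim is to recruit 60 patients across 3 sites over 2 years and randomise 1:1 to SBRT or HDR-BT", and the Sample size section says "we plan to recruit 60 patients in total (ie, 30 to each treatment arm) from three UK hospitals". The Primary outcome section fixes the time frame: "The study recruitment period is 24 months".

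Three statements then turn this target into a rate:

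- **Sample size:** "Recruiting 60 patients over 2 years, across 3 centres, would mean an average recruitment rate of 1 patient per centre per month". The text goes on to say that this information, together with the toxicity rates, will be used to judge whether a larger trial is feasible. The same section regards 30 per arm as enough to estimate toxicity for the key secondary endpoint.
- **Recruitment:** roughly two to three patients a month over the three sites together, for the same 60 patients in 24 months.
- **Primary outcome:** a steady state of recruitment is shown if "an average of two patients per month must be randomised over the remaining recruitment period". On when the clock starts, the section says "formal monitoring of recruitment will begin from the start of the patient recruitment". It also says that rates will be reported overall and for each recruiting site.

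**The concern.** Recruitment is the primary endpoint, so the planned rate and the criterion against which recruitment is judged are central figures here. Two things look wrong.

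First, the per-centre rate in the Sample size section is presented as a consequence of 60 patients, two years and three centres, with no word such as *about*. It is not the result of that division.

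Second, the Primary outcome criterion lies below the rate needed to reach 60, and the document neither says so nor explains it. Recruitment could meet the criterion while the trial ends 12 patients short and with fewer per arm than the plan calls adequate.

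What is at stake is how the result is read. Someone who sees that the criterion was met, and who has the Sample size sentence in mind, could conclude that the target rate, or even one patient per centre per month, was achieved. Neither would follow.

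**Working it through.** **Inputs**

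- Target: 60 patients, 30 per arm (Sample size)
- Recruitment period: 24 months (Primary outcome)
- Centres: 3 (abstract; Sample size)
- Stated planned rate: 1 per centre per month (Sample size)
- Stated overall rate: about 2 to 3 per month (Recruitment)
- Criterion: 2 per month on average over all sites, monitored from the start (Primary outcome)

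**Step 1. Try to reproduce the stated per-centre rate.**

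- Overall: 60 / 24 = 2.5 per month.
- Per centre: 60 / (24 × 3) = 60 / 72 = 0.83 per month.
- The stated figure is 1. Ratio: 1 / 0.833 = 1.20, so it is 20% too high.
- Working back from 1 per centre per month: 1 × 3 × 24 = 72 patients in 24 months, or 60 / 3 = 20 months to reach 60.

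The figure is not reproduced. It is recovered only by rounding 0.83 to a whole patient.

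**Step 2. Check the Recruitment section.**

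- 2 × 24 = 48 and 3 × 24 = 72; the midpoint gives 2.5 × 24 = 60.

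This statement agrees with the target.

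**Step 3. What the criterion requires.**

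- Smallest total that meets it: 2 × 24 = 48.
- Share of target: 48 / 60 = 80%; shortfall 60 − 48 = 12.
- Per centre: 48 / (24 × 3) = 0.67 per month.
- Per arm at 1:1: 48 / 2 = 24, against 30 planned.
- Time to reach 60 at this rate: 60 / 2 = 30 months.

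The criterion speaks of the remaining period although monitoring starts at the beginning. If a lead-in were meant, the number required in the monitored window would be smaller still (for example 2 × 18 = 36 over the last 18 months), so that reading does not close the gap.

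**Step 4. Effect on precision for toxicity.** Half-width of a 95% interval for a proportion, 1.96 × √(p(1 − p)/n). The toxicity rates p are assumptions, since the document gives none.

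| Assumed p | n = 30 | n = 24 | Difference |
|---|---|---|---|
| 0.5 (worst case) | 17.9 points | 20.0 points | 2.1 points |
| 0.2 | 14.3 points | 16.0 points | 1.7 points |

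**Step 5. What moving the threshold would do.** Assuming Poisson accrual:

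| True mean over 24 months | P(at least 48) | P(at least 60) |
|---|---|---|
| 48 (2.0 per month) | 0.519 | 0.052 |
| 60 (2.5 per month) | 0.951 | 0.517 |

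A threshold of 60 would fail a trial that truly accrues on target with probability 1 − 0.517 = 0.483. A floor of 48 would pass the same trial 95% of the time.

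**The case against.** The best case for the plan is as follows. The 1 is probably 0.83 rounded to a whole patient. Its inputs stand in the same sentence, the Recruitment section is compatible with 60, and no other number in the document is derived from it. Two per month is a floor, not a forecast. A floor below target is common and often sensible in a feasibility study, and it lies within the two-to-three range. The study is descriptive, with no precision target, and six fewer patients per arm costs about two percentage points of half-width.

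Most of this stands, and it rules out several stronger readings that a reader might infer:

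- *That the document carries three incompatible rates.* It does not. The target rate (0.83 per centre) and the floor (0.67) are different quantities and can coexist. The only figure in conflict with its own inputs is the 1.
- *That the wrong rate passes straight into planning of a phase III trial.* The document does not support this. Observed rates will be reported overall and by site, and these would be the natural basis for projection. The larger study described under Future work compares reirradiation with androgen deprivation alone, so these rates would not carry over directly in any case.
- *That the trial can be declared feasible on 48 patients alone.* The criterion concerns a steady state of recruitment. Feasibility also draws on toxicity rates, and compliance, withdrawal and reasons for non-recruitment are listed as further feasibility endpoints.
- *That the threshold must rise to 2.5 per month.* Step 5 shows that this is a debatable trade-off.

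Two things survive. Rounding is not declared, and taken at face value it moves the total from 60 to 72 in the quantity that the trial exists to measure. And nothing in the document identifies two per month as a deliberate minimum or relates it to the 30 per arm.

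**Conclusion.** The point holds in two parts. The planned per-centre rate in the Sample size section is misstated: it is 0.83 per month, not 1, an overstatement of 20%. The criterion in the Primary outcome section is met at 48 randomised (12 short of 60, about 24 per arm), and the document does not say that this is intended. The first part is an arithmetic error; the second is an unexplained floor, not a contradiction.

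Both results rest only on the document's own figures and on the criterion applying to all 24 months. The precision figures depend on assumed toxicity rates, and the accrual probabilities on a Poisson assumption; neither is needed for the conclusion. Severity is moderate: the figures concern the primary endpoint, but the target of 60 is consistent throughout and observed recruitment will be reported.

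**What to change.** 1. In the Sample size section, replace the per-centre figure with *2.5 patients per month, ie about 0.83 per centre per month*.
2. In the Primary outcome section, state that two per month is a minimum criterion equal to 48 patients over 24 months (about 24 per arm, 80% of target). Meeting it should then not be read as showing that the target rate for 60 patients, or 1 per centre per month, was achieved.

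The cost is two changes of wording. The target, design and analysis stay as they are, and the only downside is that the quoted per-centre rate becomes slightly less favourable.

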### Recruitment

Overall, 60 patients will be recruited over a 24-month period, approximately 2–3 patients per month (across 3 sites).

### Reporting

No formal interim analysis will take place; however, a study report will be produced for review by the independent data monitoring and ethics committee (DMEC) approximately midway through the study. The aim of the report is to evaluate and monitor the key study objectives (ie, recruitment rates, number of participants taking up their treatment allocation), as well as expected adverse events (AEs) and serious AEs and the delivery time of HDR-BT or SBRT post randomisation.

### Data collection, management and analysis

#### Withdrawal of participants

Participants who withdraw their consent to the study will be taken off the study. The research team will keep any tissue, blood, urine samples and imaging data already collected and continue analysis (unless the patient requests the destruction of samples and data). Patients will be consented from the outset to continue collecting follow-up data even if patients are withdrawn from the trial, cannot tolerate MRI scans, are unable to continue treatment or do not complete all PROM time points.

